## 6.4 Premature Termination of the Trial

Because the endpoint is assessed until 60 minutes only few patients will terminate the study prematurely: This may be patients who or whose representatives withdraw a former informed consent.

The primary statistical analysis follows the intention to treat principle as closely as possible. For a valid analysis, it is of great importance to minimise the rate of drop-outs. Therefore, in patients who do not withdraw their consent, all trial visits shall be performed as scheduled.

In case of premature termination of trial, it is necessary to document the date (as exactly as possible), the reason of termination and the current condition of the patient. Therefore, the eCRF "End of study (ES)" has to be completed for each patient. Data entry to this eCRF page will trigger an automatic report to the responsible trial team members at the ZKS Leipzig.

The "End of study"- eCRF routinely contains the following data:

- Date of individual end of trial
- Reason for trial termination

### 6.4.1 Premature Termination of the Intervention for Individual Patients

The date and if possible the circumstances and reasons for every premature termination of the therapy will be recorded by the site where the patient was being treated and will be reported to the ZKS-Data Management and the Coordinating Investigator or his deputy.

The intervention has to be stopped for any of the following reasons:

- the patient experiences a hypersensitivity or suspected allergic reaction to study treatment
- the patient experiences a medical emergency that necessitates the discontinuation of treatment
- the patient experiences a medical emergency that necessitates the unblinding of treatment
- patient withdraws his/her consent to participate
- as decision of the investigator

The discontinuation of the intervention and the circumstances must be reported in the eCRF. The study documentation will be continued unless the patient withdraws the consent for participation.

With exception of the rules described above, premature termination of therapy should be avoided.

All further trial visits will take place as planned and described in section **Fehler! Verweisquelle konnte nicht gefunden werden..**

**Termination of trial therapy does not mean that the patient is off-trial.**

### 6.4.2 Premature trial termination for individual patients

All randomised patients will be followed up until Visit 2. Premature termination of trial therapy does not necessarily lead to individual trial termination (see chapter 6.4.1 for explanation).

The only circumstances in which a premature trial termination (i.e. no further trial visits) in a randomised patient is unavoidable are:

- The clinical condition of a patient is worsening (and not responding to treatment) that contraindicates permanently participation in any trial visits

- withdrawal of informed consent or
- death of the patient.

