| VPA or LEV infusion     |                | X                                   |            |            |            |                                         |                       |                |
| GCS                | X              |                                     | X          | X          | X          |                                         |                       | X              |
| Neurological exam              | X              |                                     |            |            | X          |                                         |                       | X              |
| mRS/BI             | X  |                                     |            |            |            |                                         |                       | X              |
| Home care                      | X  |                                     |            |            |            |                                         |                       | X  |
| Adverse events                 |                | X                                   |            |            |            |                                         |                       |                |
| Recurrence seizures/SE         |                | Recorded any time until discharge   |            |            |            |                                         |                       |                |
| Clinical data     |                | X                                   |            |            |            |                                         |                       |                |

Follow-up-visit, at day of discharge or day 30

by legal or authorised representative **or** according to §41 AMG (1)

cardiopulmonary monitoring

electroencephalography, only patients with NCSE

complete blood count, liver, kidney function, sodium, level of VPA, level of LEV

Glasgow Coma Scale

modified Rankin Scale/Barthel Index

premorbid state by patient (retrospective) **or** relatives

after hospital stay (if applicable)

clinical data about the hospital stay, i.e. infections with i.v. antibiotics, special medications, initiation and duration of invasive/noninvasive ventilation, recorded on day of discharge/day 30

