**Visit 2 (V2)****Day of discharge/day before discharge from hospital or day 30 (+/- 1 day), whatever is sooner**

- Record the following data (eCRF)
  - day of recurrence of seizures or convulsive SE after successful intervention/ day of detection of NCSE (EEG) after successful intervention
  - day of first EEG-detection of terminated NCSE after failed intervention
  - further antiepileptic treatment after intervention: medication, dosage, type and frequency of application including stop of medications
  - reason for withdrawal of treatment with VPA or LEV
  - acute renal failure with or without dialysis
  - acute pancreatitis
  - acute hepatic failure
  - lab analysis: level of ammoniaemia and subsequent repetitions, as ordered by treating physician \*
  - type of infections requiring i.v. antibiotic treatment
  - start and stop of invasive/noninvasive ventilation (day)
  - development of delirium and treatment
  - complications requiring surgery or invasive diagnostics/ therapy
  - etiology of SE (cerebral focus, metabolic/infectious/toxic conditions, noncompliance/withdrawal/change of antiepileptic medication)
  - home care after hospital stay (if applicable)
- Administer GCS and perform brief neurological exam: orientation, horizontal extraocular movements, motor drift of both arms and legs, sensation, language.
- Obtain mRS and BI

\* **NOTE:** As soon as an otherwise unexplained disturbance of consciousness, nausea or hypotension occurs in duration of treatment with VPA during the hospital stay the efforts of clarification **must** include the detection of a potential hyperammonemia.

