#### 7.1.3 Documentation and Reporting

Adverse events (AE) will be documented for patients in both treatment arms (VPA and LEV) **from the moment of initiating the infusion of IMPs until the end of the study.**

AE reports comprise any newly reported events as well as worsening of pre-existing conditions (i.e. increased intensity/grading) during the predefined reporting period of events.

AEs are documented on specified AE forms provided in the CRF.

If an AE fulfils any of the criteria for an SAE (see chapter 7.4 for SAE-definition), both the AE pages of the CRF **and** the SAE form must be completed. This applies to all SAEs, **whether or not they are considered to be related to trial treatment.**

For both serious and non-serious AEs, documentation should be supported by an entry in the patient's health record. Required information in the patient's health record should include:

- type of AE
- grade/severity/intensity acc. to e.g. NCI CTCAE 5.0
- seriousness (see also section 7.4)
- onset date

- end date
- actions required
- outcome
- assessment of its relationship to trial drug

All abnormal physical and/or laboratory results which are considered to be clinically relevant by the investigator should be recorded as AEs. If an abnormal laboratory result meets any of the criteria for a SAE, this must also be reported on the SAE Form.

Adverse Events are classified by their seriousness, intensity/severity and relationship to the IMP (see also 16.1).

The following events could be SE-related clinical outcomes/endpoints. Occurrence will be documented as (S)AEs and furthermore within the CRF in addition and independently from the (S)AE-form:

- Indication for the need of an emergency medication (different from allocated study drug) during 60 minutes after initiation of infusion
- Respiratory depression requiring noninvasive/invasive ventilation (oxygen supply excluded) during 60 minutes after initiation of infusion
- SE-recurrence/seizures after successful intervention
- SE- associated ventilation until hospital discharge
- Delirium
- Infections treated with i.v. anti-infectives (type of infection)
- Other complications: sedation, dizziness nausea, vomiting, new thrombocytopenia, leukopenia, new elevation of liver enzymes, acute new liver failure or pancreatic damage, hyperammonaemia, tremor, psychiatric complications.

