#### Determination of primary and secondary measures

All clinical scales (GCS, mRS, BI) are validated and widely used in clinical settings and / or clinical trials. They will be performed by trained neurologists. The pre-mRS and pre-BI reflect the functional status of the patient before the admission to the hospital and will be scored by the patient or a close relative if the patient's capability is impaired. Recurrence of SE or seizures during the hospital stay is defined as witnessed convulsions with or without

impairment of consciousness in case of CSE and the detection of ictal EEG activity in case of NCSE. SE-associated mortality includes all cases of death during the hospital stay even if they are not directly related to SE. The necessity to invasive ventilation is defined as the proportion of patients who have to be ventilated during the hospital stay.

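### Section 6.4.2 ends trial visits for patients who worsen, against section 6.4, so Visit 2 function scores can go missing in the sickest survivors

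*Protocol*

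**What the plan says.** Section 6.4 asks for drop-outs to be kept to a minimum and requires that "in patients who do not withdraw their consent, all trial visits shall be performed as scheduled". Section 6.4.2 opens in the same spirit: "All randomised patients will be followed up until Visit 2". It then names three circumstances in which ending all further visits cannot be avoided: withdrawal of consent, death, and "The clinical condition of a patient is worsening (and not responding to treatment) that contraindicates permanently participation in any trial visits".

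When a patient ends the trial early, section 6.4 asks for the date, "the reason of termination and the current condition of the patient".

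The only visit after the first 24 hours is Visit 2 (section 6.3), on or just before the day of discharge or at day 30, whichever is sooner. There the site is to "Obtain mRS and BI", repeat the GCS and a brief neurological examination, and enter hospital-stay data. According to the Schedule of Assessments these include "initiation and duration of invasive/noninvasive ventilation, recorded on day of discharge/day 30".

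**The concern.** Two rules apply to a patient who deteriorates but has not withdrawn consent. Section 6.4 says the visit takes place; section 6.4.2 says it does not. A site following 6.4.2 would skip Visit 2.

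That loss depends on the outcome being measured, because the patients removed are those doing worst. By then the arm is known: section 8.1.1 unblinds treatment after 60 minutes at the latest. If exit is commoner in one arm, that arm's functional results look better than they are.

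This bears on the trial's interpretation. Section 1.2.1 foresees that an efficacy advantage of one drug may be offset by the safety of the other, and section 8.2.2 wants efficacy and safety given equal weight.

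**Working it through.** **1. The rules side by side**

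| Place | Who may miss Visit 2 |
|---|---|
| 6.4 | Only patients who withdraw consent |
| 6.4.1 (intervention stopped early) | Documentation continues unless consent is withdrawn; later visits go ahead as planned |
| 6.4.2, opening sentence | Nobody who was randomised |
| 6.4.2, list | Withdrawal, death, or worsening that does not respond to treatment |

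Death is a self-evident exception. Worsening is not, and it conflicts with 6.4.

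**2. What is lost if Visit 2 is skipped**

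- mRS and BI: the Schedule has them at screening (premorbid state) and at Visit 2 only. No other post-treatment value exists.
- GCS and neurological examination: the last earlier assessment is at 60 minutes.
- Ventilation, delirium, infections treated intravenously, and recurrence: section 7.1.3 also has these documented as (S)AEs, for example "SE- associated ventilation until hospital discharge".
- Death: section 7.4.2 has SAEs documented to the end of the study. Section 16.1.5 requires the fatal event to be reported even when death comes four weeks after medication. The endpoint is inclusive: "SE-associated mortality includes all cases of death during the hospital stay even if they are not directly related to SE". Section 8.2.2 gives death an mRS score of 6, so the score follows from the death report.

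The unprotected data are therefore mRS, BI and the late examinations in patients who exit and survive.

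**3. Does the 5% drop-out figure limit this?**

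Section 8.4 expects at most 5% drop-outs and cites 6.4.2. Its figure reproduces: 454 × 1.05 = 476.7, so 477 randomised; 477 − 454 = 23, and 23/477 = 4.8%. But section 3.3 defines the 454 as evaluable for the primary analysis, which is complete at 60 minutes. The list in 6.4.2 also contains death, and section 4.3 cites an overall SE mortality of 20%. At anything near that level, deaths alone would exceed 5%. The 5% can describe loss before 60 minutes; it does not bound loss at Visit 2.

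**4. Would the missing-data plan repair it?**

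Section 8.5.2 envisages multiple imputation only if a high proportion of questionnaire data is missing. A few percent need not trigger it. If triggered, imputation assuming data missing at random would draw on values recorded before the deterioration and would not recover its effect.

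**5. Size, by illustration**

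The documents give no exit rate and no rate of poor function, so all inputs here are assumptions. Among survivors, let the true rate of poor function be p = 0.40 in both arms, and let a share e of those patients exit for worsening.

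Observed rate = p(1 − e) / (1 − pe)

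| e, arm A | e, arm B | Observed A | Observed B | A − B (points) | Missing overall |
|---|---|---|---|---|---|
| 5% | 5% | 38.8% | 38.8% | 0 | 2% |
| 10% | 10% | 37.5% | 37.5% | 0 | 4% |
| 12.5% | 0% | 36.8% | 40.0% | −3.2 | 2.5% |
| 20% | 5% | 34.8% | 38.8% | −4.0 | 5% |
| 25% | 10% | 33.3% | 37.5% | −4.2 | 7% |

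Fourth row: A is 0.40 × 0.80 / (1 − 0.08) = 0.32/0.92 = 0.348; B is 0.40 × 0.95 / (1 − 0.02) = 0.38/0.98 = 0.388; missing overall is (0.08 + 0.02)/2 = 0.05.

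Equal exit lowers both rates without a spurious difference. Unequal exit creates one of 3 to 4 points in these examples.

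**The case against.** The exit is narrowly worded: deterioration must permanently rule out taking part in any visit. Since Visit 2 is largely chart abstraction, that condition should seldom be met, and section 6.4 itself expects few early terminations. Section 8.4 calls the secondary analysis mainly explorative. All of this stands and limits the size. It does not settle which rule a site follows, and the text offers no criterion for when the condition is met.

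Within 6.4.2, the opening sentence can be read as a general rule followed by its exceptions. That is fair; the clear contradiction is with section 6.4.

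A reader might infer that deaths and ventilation also go missing, so that mortality is understated. The documents do not support this. Both have the (S)AE routes set out above, section 6.4.2 ends visits rather than safety reporting, and section 3.4 defines the formal end of the study as the last patient's last visit. A gap opens only if a site takes the end of the study to mean the individual's exit date. That misreading is possible: section 7.4.2 equates the end with Visit 2, which an exited patient never has, and the end-of-study form asks for the date of the individual's end of trial. It is a reason to clarify the wording, not a basis for a mortality figure.

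**Conclusion.** The point holds for functional outcome and late examinations in surviving patients. Section 6.4.2 contradicts section 6.4, and following it loses mRS, BI, late GCS and the late neurological examination where they are likely to be worst, with the arm known. The planned imputation does not cure this.

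The size cannot be fixed from the documents. Under the assumed 40% rate of poor function, the spurious arm difference runs from zero with equal exit to about 4 points with the unequal shares shown. These are examples, not bounds.

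The primary endpoint, its sample size and its power are unaffected. Deaths, ventilation, delirium, infections and recurrence are at risk only under the misreading of the end of the study, and no bias in mortality is claimed. The change is worth making because the missingness depends on outcome and is easily avoided.

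**What to change.** Remove clinical worsening from the list in section 6.4.2, so that only withdrawal of consent or death ends participation, as section 6.4 implies.

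Add that for every other patient the Visit 2 data (mRS, BI, ventilation, complications and vital status) and SAEs are recorded up to discharge or day 30, from the chart, treating staff or a proxy where the patient cannot take part. Two details go with this:

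- The Visit 2 list in section 6.3 has no vital-status item, so one should be added.
- Section 8.2.2 has the scales performed by trained neurologists, so the text should allow scoring from these sources and have the source noted. Relatives or a proxy are already accepted for the premorbid mRS and BI.

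In sections 7.1.3 and 7.4.2, state that collection runs to discharge or day 30 whatever the date on an individual end-of-study form. In section 8.4, say that the 5% refers to loss before the 60-minute endpoint.

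The cost is one deleted bullet, a few clarifying sentences and slightly more chart abstraction in a few patients. No extra visit is needed.

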## 6.5 Plan for Further Treatment

Beyond the single infusion the treatment of SE is determined by the responsible clinicians and follows clinical standards. The possible further treatment with one of the trial drugs VPA or LEV will be observed according to the study design.

## 7 ADVERSE EVENTS (AE/SAE)

### 7.1 Adverse Events (AE)

#### 7.1.1 Definition Adverse Event

An Adverse Event (AE) is any untoward medical occurrence in a patient or clinical investigation subject administered a pharmaceutical product and which does not necessarily have to have a causal relationship with this treatment (ICH-Guideline E2A).

Adverse Events encompass any unfavourable and unintended sign (including an abnormal laboratory finding, for example), symptom, or disease that arise newly or worsen after the inclusion of the patient into the trial.

#### 7.1.2 Definition Adverse Reaction

In the pre-approval clinical experience with a new medicinal product or its new usages, particularly as the **therapeutic dose(s) may not be established**: all noxious and unintended responses to a medicinal product related to any dose should be considered adverse drug reactions. The phrase "responses to a medicinal products" means that a causal relationship between a medicinal product and an adverse event is at least a reasonable possibility, i.e., the relationship cannot be ruled out (ICH Guideline E2A).

#### 7.1.3 Documentation and Reporting

Adverse events (AE) will be documented for patients in both treatment arms (VPA and LEV) **from the moment of initiating the infusion of IMPs until the end of the study.**

AE reports comprise any newly reported events as well as worsening of pre-existing conditions (i.e. increased intensity/grading) during the predefined reporting period of events.

AEs are documented on specified AE forms provided in the CRF.

If an AE fulfils any of the criteria for an SAE (see chapter 7.4 for SAE-definition), both the AE pages of the CRF **and** the SAE form must be completed. This applies to all SAEs, **whether or not they are considered to be related to trial treatment.**

For both serious and non-serious AEs, documentation should be supported by an entry in the patient's health record. Required information in the patient's health record should include:

- type of AE
- grade/severity/intensity acc. to e.g. NCI CTCAE 5.0
- seriousness (see also section 7.4)
- onset date

- end date
- actions required
- outcome
- assessment of its relationship to trial drug

All abnormal physical and/or laboratory results which are considered to be clinically relevant by the investigator should be recorded as AEs. If an abnormal laboratory result meets any of the criteria for a SAE, this must also be reported on the SAE Form.

Adverse Events are classified by their seriousness, intensity/severity and relationship to the IMP (see also 16.1).

The following events could be SE-related clinical outcomes/endpoints. Occurrence will be documented as (S)AEs and furthermore within the CRF in addition and independently from the (S)AE-form:

- Indication for the need of an emergency medication (different from allocated study drug) during 60 minutes after initiation of infusion
- Respiratory depression requiring noninvasive/invasive ventilation (oxygen supply excluded) during 60 minutes after initiation of infusion
- SE-recurrence/seizures after successful intervention
- SE- associated ventilation until hospital discharge
- Delirium
- Infections treated with i.v. anti-infectives (type of infection)
- Other complications: sedation, dizziness nausea, vomiting, new thrombocytopenia, leukopenia, new elevation of liver enzymes, acute new liver failure or pancreatic damage, hyperammonaemia, tremor, psychiatric complications.

## 7.2 Safety Analysis

During the course of the trial, every patient will be monitored closely. Before the initiation of the infusion and during 60 min following initiation of the infusion the following safety assessments will be performed:

- Neurological assessments
- Cardiopulmonary monitoring during the whole time of infusion until 60 minutes after initiation of infusion
- Laboratory assessments before and 60 minutes after initiation of infusion
- Furthermore safety monitoring encompasses documenting Adverse Events. Adverse Events will be reported until the end of the study.

## 7.3 Concomitant Diseases

At screening all relevant ongoing or past diseases or medical conditions will be recorded as detailed as possible. Deterioration of a pre-existing condition during the trial will be reported as an adverse event.

## 7.4 Serious Adverse Events/Serious Adverse Reactions (SAE/SAR)

### 7.4.1 Definition

An Adverse Event/Reaction is defined to be serious according to ICH-Guideline E2A, paragraph IIB  §3 (8) GCP-V , if it

- results in death,
- is life-threatening,

Note: The term “life-threatening” in the definition of “serious” refers to an event in which the patient was at risk of death at the time of the event; it does not refer to an event which hypothetically might have caused death had it been more severe.

- requires in-patient hospitalisation or prolongation of existing hospitalisation,
- results in persistent or significant disability/incapacity or
- is a congenital anomaly/birth defect .

Medical and scientific judgement should be exercised in deciding whether expedited reporting is appropriate in other situations, such as important medical events that may not be immediately life-threatening or result in death or hospitalisation but may jeopardise the patient or may require intervention to prevent one of the other outcomes listed in the definition above. These should also usually be considered serious.

